### Handling missing data

Missing data will be handled using multiple imputation, which ensures that all observed values in the set are retained.^50 51^ The multiple imputation will be conducted using an unconstrained two-level model in Mplus V.8,^52^ with person-years nested within persons.

### Statistical analysis

Discrete-time event history analysis^53^ will be conducted to examine whether changes in the probability of youth smoking transitions are associated with the implementation of the smoke-free public places legislation (Q1). The implementation of smoke-free legislation is viewed as a natural experiment,^41 54^ and analyses will examine if there is a step change or change in trend in the probability of smoking transitions after the country-specific implementation dates for the smoke-free legislation (ie, 2006 for Scotland, 2007 for the rest of the UK). Youth will only be considered at risk for a transition once they have made the previous transition (ie, they are only at risk for experimentation once they have tried smoking). Thus, data for each analysis will be right censored at the year of the smoking transition (or age 15 years) and left censored prior to the previous transition (or age 11 years). Escalation to daily smoking and quitting will be treated as two alternative outcomes, which young people will be at risk of once they commence occasional smoking. In line with previous work,^47^ youths who skipped smoking transition stages will be treated as making the intervening transitions in the same year. For instance, youths who transited from never having tried smoking to ex-smoker in the same year will be treated as having progressed to occasional smoker and having quit within the same year (but not as having escalated to daily smoking). Analyses will be adjusted for age, gender, the overall temporal trend in rates (which may encompass effects of other temporal increases in tobacco control) and overall differences in rates between UK countries.

We will then examine whether any effects observed on youth smoking transition differ by socioeconomic position (Q2). Parental education level will be used as an indicator of socioeconomic position. In cases where parental educational qualification for both parents differs, the higher qualification will be used. This will be added to the predictive models, alongside interactions with the variables representing the implementation of the legislation.

A multilevel logistic regression model (with person-years nested within persons) will be used to investigate whether there is a step change or change in trend for the prevalence of parental smoking (any current smoking by either parent) after smoke-free public places legislations were implemented in the UK (Q3A) and whether observed changes (if any) differ by socioeconomic position (Q3B). This model will include all years of data for all respondents without any right or left censoring and will be adjusted for the young person’s age, gender, the overall temporal trend in parental smoking and overall differences between UK countries. The second stage of the modelling will additionally include parental education and interactions between parental education and the variables representing the implementation of the legislation.

Next, building on the models developed to assess whether the impact of the legislation on youth smoking transitions varied by socioeconomic position (Q2), parental smoking will also be included and we will assess whether this explains any observed differences associated with the implementation of the legislation (Q4A). We will test for interactions between parental smoking and the variables representing the implementation of the legislation to see if the influence of parental smoking changes after the legislation (Q4B) and then for a three-way interaction between parental smoking, legislation implementation and socioeconomic position to see if this varies by socioeconomic position (Q4C).

A final step will be to adjust the above models for relevant factors that may be associated with the implementation of the legislation. This will include annual levels of cigarette taxation, the change in the legal age of purchase for cigarettes from 16 to 18 in 2007 for England, Wales and Scotland, and in 2008 for Northern Ireland (ie, the implementation date differs from that of the smoke-free legislation by 1 year in Scotland and Northern Ireland), and survey estimates of the annual prevalence of e-cigarettes from 2012^55^ (with e-cigarette prevalence coded as 0 prior to that date). As an additional sensitivity test, we will rerun analyses with the date of ban implementation transposed either 5 years forward or backward in time. If observed effects are genuinely attached to the ban rather than overall temporal trends, these transposed ‘placebo’ effect estimates should be weaker or null compared with those observed at the actual ban implementation dates.

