### Data

Data from the British Household Panel Survey (BHPS) Youth Sub-Sample and Understanding Society, both of which are freely available to bona fide researchers from the UK Data Archive under their normal terms and conditions,^48 49^ will be used in this study. Both Understanding Society and BHPS studies obtained consent for data sharing from their participants. More information on the data sources, consent and sampling can be found on BHPS and Understanding Society websites https://www.iser.essex.ac.uk/bhps and https://www.understandingsociety.ac.uk/, respectively. Data on youths’ (11–15 year olds) and parents’ smoking history, and parents’ socioeconomic position from the BHPS (covering the period 1994–2009) will be merged with those of the recent Understanding Society Survey (from 2009 to 2016). The merger of these datasets gives coverage of the period from 1994 to 2016, with data from 2016 newly released in November 2017. As such, 9–10 years of postlegislation data will be available in the dataset. This amount of postlegislation data will be important in investigating the immediate as well as the long-term impact of the smoke-free public places legislation on youths smoking transition. Respondents will be included for each year they were aged 11–15 within this period (ie, a maximum of 5 years of data per respondent).

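### The ban varies only by country and calendar year, but the models as described carry no year-level error term, so intervals for the ban main effects (Q3A explicitly; Q1 and Q4A if fitted as listed) are too narrow

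*Protocol article*

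**What the plan says.** All of this is in the Protocol article.

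- **Exposure.** Statistical analysis gives the ban dates as "2006 for Scotland, 2007 for the rest of the UK". It sets the Q1 targets, a step and a change in trend at those dates: "analyses will examine if there is a step change or change in trend in the probability of smoking transitions after the country-specific implementation dates".
- **Length of series.** The Data section states: "The merger of these datasets gives coverage of the period from 1994 to 2016".
- **Q1 model terms.** "Analyses will be adjusted for age, gender, the overall temporal trend in rates", together with "overall differences in rates between UK countries". No error structure is given for these event-history models.
- **Q3 model.** "A multilevel logistic regression model (with person-years nested within persons) will be used" for parental smoking, again adjusted for an overall trend and country differences. Here the nesting is stated, and it stops at the person.
- **Imputation.** Handling missing data specifies "an unconstrained two-level model in Mplus V.8", with the same two levels.
- **Later steps.** The last paragraph of Statistical analysis adds annual cigarette taxation, the legal-age change and annual e-cigarette prevalence as covariates. It also reruns the analyses with the ban date moved five years either way.

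**The concern.** A variable that switches once per country carries information only at the level at which it switches. Exposure status differs between countries in one year, 2006, so the step and slope change are in effect estimated from one series of 23 annual points. If the rate in a given year lies off the fitted trend for reasons shared by everyone surveyed that year, that deviation does not shrink as respondents are added. A model with person-level error alone treats it as noise that does shrink.

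The article itself gives reasons to expect such deviations. The Introduction describes incremental tobacco control, ongoing tax changes and growing e-cigarette use, and the Data section joins two surveys at 2009, inside the post-ban period.

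At stake is whether a reported step or trend change in youth transitions or parental smoking is distinguishable from ordinary year-to-year movement. There are four transitions with two ban terms each, so even a moderate excess of false positives matters.

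**Working it through.** The article states no sample size, standard error or power, so there is no figure to reproduce. The check fits the model as described and asks how wrong its standard error is when years vary.

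**Inputs from the article**
- Years: 2016 − 1994 + 1 = 23. Cells: 4 × 23 = 92.
- Outside Scotland: 13 pre-ban years (1994–2006) and 10 post-ban years (2007–2016), counting the year of implementation as post-ban.
- Terms: country, overall trend, step, slope change.

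**Assumed inputs (not in the article)**
- Linear trend.
- Person-years at risk split 65/13/14/8% over England, Wales, Scotland and Northern Ireland.
- 300, 1,000 or 2,500 person-years at risk per year.
- Annual hazard 10%.
- Year shock common to all countries, SD 0.05 or 0.10 on the logit scale.
- Two-sided 5% test.

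**Formulas.** With design matrix X, weights W = n·p(1−p) per cell and year-shock covariance V:
- Model variance: A = (X′WX)⁻¹.
- True variance: A + A·X′WVWX·A.
- Ratio r = true SE / model SE.
- False-positive rate = 2·[1 − Φ(1.96/r)].

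**Worked case: step, 1,000 per year, SD 0.10.** The model SE is 0.0876. The year shock adds a component of 0.0797, and this component is the same at every sample size. True SE = √(0.0876² + 0.0797²) = 0.118, so r = 0.118/0.0876 = 1.35. The false-positive rate is 2·[1 − Φ(1.96/1.35)] = 14.7%.

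**Step, all cases**

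| Person-years at risk per year | Model SE | r at SD 0.05 / 0.10 | False positives at SD 0.05 / 0.10 |
|---|---|---|---|
| 300 | 0.160 | 1.03 / 1.12 | 5.7% / 7.9% |
| 1,000 | 0.088 | 1.10 / 1.35 | 7.4% / 14.7% |
| 2,500 | 0.055 | 1.23 / 1.75 | 11.2% / 26.3% |

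The slope change gives almost the same: 7.6% and 15.4% at 1,000 per year. With SD 0 the rate is 5.0%. A Monte Carlo check (1,500 runs) of the step at SD 0.10 gave 15.5% at 1,000 per year and 7.4% at 300.

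**Shocks independent between countries.** At 1,000 per year and SD 0.10 the step rate falls from 14.7% to 10.0%.

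**Parental smoking (Q3A).** Assume prevalence 35%, 1,000 youths per year, and a design effect of 1 to 3 as a rough stand-in for repeated measures. This is not a fit of the random-intercept model. The step rate runs from 7.0% (design effect 3, SD 0.05) to 26.5% (design effect 1, SD 0.10).

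**Interactions.** Split each cell into two education groups that share the same year shock. The SE ratio for the education-by-ban step and slope terms is 1.00, so their rate stays at 5.0%. A simulation of the same comparison at 1,000 and 3,000 per year, with SD 0.05 to 0.15, rejected in 4.0–6.1%.

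**The case against.** **Scope.** A reader might infer that every ban term from Q1 to Q4 has too small a standard error, including the inequality results that are the project's stated aim. The plan does not support that. Q2, Q3B, Q4B and Q4C are interactions of the ban with education or parental smoking, and a shock shared by the groups cancels in them. They are affected only if shocks differ by group, which the article gives no figures to judge.

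**Silence on Q1.** The article names no error structure for the event-history models, and a fuller analysis plan could include a year term. This stands: for Q1 and Q4A the point is conditional on fitting the listed terms only. It does not remove the point for Q3A, where the nesting is written down, although parental smoking is a secondary outcome.

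**Size.** Risk sets are restricted: experimentation needs prior trying, and escalation and quitting need occasional smoking. If those sets number a few hundred per year, the excess is small (5.7–7.9% at 300). This also stands.

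**Existing safeguards.** The year-varying covariates absorb the fluctuation that they explain, and the article does not say that the trend is linear, so a flexible trend could absorb slow departures. The placebo dates can expose an effect that is not tied to the ban. These lower the risk of a false ban claim. They do not put the remaining year variance into the standard errors, and the placebo check offers two comparison dates judged with the same standard errors.

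**Conclusion.** The point holds for the ban main effects: the step and trend change in Q3A as specified, and in Q1 and the ban terms compared in Q4A if those models contain only what is listed. The direction does not depend on the assumptions: any positive year-level variance around the fitted trend makes these intervals too narrow, and more so with larger samples.

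The size does depend on them. It ranges from negligible for a transition with few at risk and a quiet series, to a false-positive rate of about a quarter for large risk sets, or for parental smoking, at a year SD of 0.10. It is lower if shocks are independent between countries. The inequality and effect-modification interactions are not shown to be affected. The change should be made before the models are fitted.

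**What to change.** - Add a random intercept for calendar year, and for country-by-year where estimable, to the Q3A model and to the Q1 and Q4A transition models.
- Base degrees of freedom for the step and slope change on the number of years. With 23 years and four terms in the time series (intercept, trend, step, slope change), 23 − 4 = 19, so the critical value is about 2.09, not 1.96.
- As a check, regress the adjusted country-year rates on the step and trend terms with autocorrelation-robust errors.
- Do not use year fixed effects for this purpose. Exposure status differs between countries only in 2006, so the step would rest on that single year.

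The cost is one or two extra variance terms and wider confidence intervals for the ban main effects. At 1,000 person-years per year, the assumed inputs imply step intervals 1.10 to 1.35 times as wide, before the change in critical value. No new data are needed.

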## Methods and analysis

### Study design

The study will constitute secondary analyses of UK survey data (see section on Data). The control group will be all UK youths aged 11–15 years prior to the implementation of the smoking ban (in 2006 for youths living in Scotland and 2007 for those living elsewhere in the UK). The intervention group is all UK youths aged 11–15 years after the implementation of the ban. The primary outcomes of interest are the rates of initiation, experimentation, escalation to daily smoking and quitting within this age group. A secondary outcome of interest is the prevalence of smoking among parents of these youths. The causal interpretation of the differences between these groups rests on the assumption that the implementation of the smoke-free public places legislation is the only relevant difference between these groups and that there are no other systematic differences between these groups that would account for their differences in outcomes.

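### The later-stage models mix part-exposed entry years with full years and list no term that marks them, so a ban effect on initiation can leak into the ban terms for experimentation, escalation and quitting

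*Protocol article*

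**What the plan says.** All quotes are from the protocol article. Under Study design: "The primary outcomes of interest are the rates of initiation, experimentation, escalation to daily smoking and quitting within this age group". The Statistical analysis section then sets out the discrete-time risk sets:

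- Start of risk: "Youth will only be considered at risk for a transition once they have made the previous transition", with data "left censored prior to the previous transition (or age 11 years".
- End of risk: "right censored at the year of the smoking transition (or age 15 years".
- Stages passed within one year: "youths who skipped smoking transition stages will be treated as making the intervening transitions in the same year".
- Occasional smokers: "Escalation to daily smoking and quitting will be treated as two alternative outcomes".
- Adjustment: "Analyses will be adjusted for age, gender, the overall temporal trend in rates", together with differences between UK countries.

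The Data section allows "a maximum of 5 years of data per respondent". The question 2 models add parental education and its interactions with the ban variables. No transition rate or entry-year share is given.

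**The concern.** Only years before the previous transition are removed, and a later-stage event may fall in the entry year, so that year is a row in the later-stage risk set. A youth who first tries a cigarette partway between two annual interviews can progress only in what is left of that year. The row still counts like any later full year and shares the same baseline probability at a given age.

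This matters because the quantity that sets the entry-year share is one the study expects the ban to change. If initiation falls or shifts to other ages after the ban, the mix of entry years and full years among triers of a given age changes too. The experimentation model can then show a step or trend although experimentation has not changed. The same route is open for escalation and quitting after entry to occasional smoking, and for the education interactions if entry timing shifts unequally by education.

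The Discussion promises to show which stages the legislation affects, and this leakage blurs that attribution. Moving the ban date by five years is not designed to detect it, because the artefact is tied to the real date.

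**Working it through.** The plan gives no figure to reproduce. Every hazard below is an assumption, and only experimentation was modelled.

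**Inputs from the article:** ages 11–15, data for 1994–2016, ban in 2007 (2006 in Scotland, ignored in the main calculation), the risk-set rules above, and adjustment for age and linear trend.

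**Assumed inputs:** initiation hazards of 6, 8, 12, 16 and 18% at ages 11 to 15, nobody having tried before 11; a later-stage rate λ of 0.2, 0.4 or 0.7 per year; entry uniform within the year; entry-year hazard k times the later hazard; no true ban effect on experimentation.

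**Formulas**

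- Full-year probability: 1 − exp(−λ).
- Entry-year probability: 1 − (1 − exp(−kλ))/(kλ).
- Pooled probability: s × entry-year + (1 − s) × full-year, where s is the entry-year share of risk-years.

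**Step 1, one worked case (λ = 0.4, k = 1).** Full year: 1 − exp(−0.4) = 0.330. Entry year: 1 − 0.330/0.4 = 0.176 (from unrounded values). With s = 0.49, pooled = 0.49 × 0.176 + 0.51 × 0.330 ≈ 0.254. Over the three rates, s is 44–56%, and pooled against full-year probabilities are 0.143 v 0.181, 0.254 v 0.330 and 0.379 v 0.503.

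**Step 2, how far age separates the rows.** In these calculations every age-11 row is an entry year. By age 15 the share is 9–59%, depending on the entry profile assumed. Age therefore tracks entry years but does not identify them.

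**Step 3, ban terms.** Expected counts were fitted by logistic regression on age dummies, linear year, ban step and ban slope. The true ban odds ratio (OR) is 1. The delay scenario multiplies initiation by 0.5, 0.5, 0.7, 1.2 and 1.4 at ages 11 to 15.

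| k | Entry-year v full-year probability (λ = 0.4) | Pooled v full-year, all λ | False step OR, initiation cut 20–40% | False step OR, initiation delayed |
|---|---|---|---|---|
| 1 | 0.176 v 0.330 | 21–25% lower | 1.02–1.05 | 0.95–0.96 |
| 1.5 | 0.248 v 0.330 | 11–15% lower | 1.01–1.03 | 0.98 |
| 2 | 0.312 v 0.330 | 1–5% lower | 1.00–1.01 | 0.99–1.00 |
| 3 | 0.418 v 0.330 | 11–18% higher | 0.98–0.99 | 1.01–1.02 |

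With no change in initiation, step and slope are exactly 1.00 at every k. In the delay scenario at k = 1 the slope is 0.993 per year. After nine years (the Data section expects 9–10 post-ban years) this gives about 0.96 × 0.993^9 = 0.90.

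**Step 4, other entry profiles.** A second calculation used six age profiles of entry, annual later-stage probabilities of 0.1 to 0.5 and a country term. The pooled shortfall at constant hazard was 13–29%. For the ban terms:

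- Entry 10–30% lower after the ban: step OR 1.01–1.03, nine-year trend OR 0.94–0.99.
- Entry halved: step OR 1.04–1.07, nine-year trend OR 0.89–0.93.
- Entry delayed: step OR 0.92–0.98.

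**Step 5, with an entry-year indicator.** Step and slope return to 1.000. This is built in, because entry year is the only omitted predictor in the assumed model. It shows that the indicator targets the mechanism, not that real data would be free of bias.

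**The case against.** **The level is not the target.** Questions 1 and 2 ask about a step or trend change at the ban. A probability per survey year among those in the risk set is a legitimate quantity, and a level error that is the same before and after the ban leaves the ban terms alone. This stands. The point rests on a shift in entry, not on the level.

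**Progression may be fastest just after entry.** The same-year rule exists because youths can pass several stages in one year. At twice the later hazard the artefact nearly vanishes, and beyond that it changes sign. This also stands, so no single size or direction can be claimed. It does not make the mixture harmless: that requires the two forces to cancel or entry timing never to move.

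**A condensed article may leave the coding of time to a fuller plan.** This stands in part, since nothing in the article rules out a duration term. But the article does state its risk set and its adjusters, and the suggestion addresses those.

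**Two stronger readings are tempting.** A reader might infer that the three later-stage rates are biased by more than 20%. The article supplies no hazards, the assumed inputs fall on both sides of 20%, the sign can reverse, and escalation and quitting were not modelled. A reader might also take the first risk-set sentence to mean that risk starts the year after entry, so that same-year events lack a matching denominator. The rule removing only earlier years, together with the same-year rule, keeps the entry year in, so the text does not support that reading.

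**Conclusion.** The point holds as a modest, conditional weakness. The later-stage risk sets include entry years as ordinary years, and the listed adjusters mark them only in part. If the ban alters the level or timing of initiation, the later-stage ban terms can move without any change in progression.

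For experimentation, with a constant hazard and entry uniform within the year, the main calculation puts the false step OR at 1.02–1.05 for a 20–40% cut in initiation and 0.95–0.96 for a delay. These figures are illustrations under assumed inputs. They shrink to about 1.00 at twice the entry-year hazard and reverse direction at three times. If entry does not change, the ban terms are unbiased by this route. No figure is offered for escalation, quitting or the education interactions, where the argument is one of mechanism only. The case for acting is that the remedy is cheap and works for either sign.

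**What to change.** In the Statistical analysis section, add time since the previous transition to the experimentation, escalation and quitting models alongside age. The minimum is an indicator for entry year against later years. When rates for these stages are reported, show entry-year and later-year probabilities separately.

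The cost is one extra parameter in each of three models (for the indicator) and slightly less precision. The indicator comes from data already held, and the initiation model is unchanged.

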**Figure 2 F2:**
[figure not shown]
Smoking stages for early adolescents. Adapted from ‘Socioeconomic position and early adolescent smoking development: evidence from the British Youth Panel Survey (1994–2008)’ by Green *et al*.^47^

Using population representative longitudinal survey data, we will address the following research questions:Q1. Has the implementation of the smoke-free public places legislation in the UK been associated with a step change or change in the trend in the probability of youth smoking transitions?Q2. Has the implementation of the smoke-free public places legislation in the UK been associated with a step change or change in the trend in the inequalities in the probability of youth smoking transitions?Q3. (A) Has the implementation of the smoke-free public places legislation in the UK been associated with a step change or change in the trend in the prevalence of smoking among parents of UK youths? (B) Does the observed change (if any) differ by socioeconomic position?Q4. (A) Do changes in parental smoking explain any impact of the smoke-free public places legislation on the probability of youth smoking transitions? (B) Has the implementation of the smoke-free public places legislation in the UK been associated with any change in the strength of the association between parental smoking and the probability of youth transitions? (C) Does the observed change (if any) differ by socioeconomic position?Q5. How distinct are the impacts of the smoke-free public places legislation from the impacts of the change in the legal age for purchasing tobacco, the increasing prevalence of e-cigarettes and the changes in tobacco taxation on youth smoking transition?

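### The inequality models let education and parental smoking modify only the ban terms, so a gap already drifting before the ban is reported as a ban effect

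*Protocol article*

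**What the plan says.** All of this is in the protocol article, Statistical analysis, apart from the research questions.

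- **Youth models (Q1).** "analyses will examine if there is a step change or change in trend in the probability of smoking transitions after the country-specific implementation dates". The time trend is a separate adjustment item: "Analyses will be adjusted for age, gender, the overall temporal trend in rates".
- **Education (Q2).** Parental education enters as a main effect, and then: "This will be added to the predictive models, alongside interactions with the variables representing the implementation of the legislation".
- **Parental smoking as outcome (Q3B).** The base model adjusts for "the overall temporal trend in parental smoking and overall differences between UK countries". The second stage will "additionally include parental education and interactions between parental education and the variables representing the implementation of the legislation".
- **Parental smoking as moderator (Q4B, Q4C).** "We will test for interactions between parental smoking and the variables representing the implementation of the legislation", "then for a three-way interaction between parental smoking, legislation implementation and socioeconomic position".

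No model is given a term for education by time or parental smoking by time. Yet Q2, in the research questions, asks about "a step change or change in the trend in the inequalities in the probability of youth smoking transitions".

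**The concern.** A change in the trend of inequality can be estimated only against a pre-ban trend of inequality, and the model as described has none. Education may shift the level of the outcome, the step at the ban and the slope after it, but not the slope before it. Between 1994 and the ban the fitted gap is a constant. If the real gap was moving over those years, the ban interactions are the only terms that can absorb the movement.

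Inequality is the project's stated aim. The Introduction describes tobacco control tightening step by step over the period, so a constant gap is something to test rather than impose. The Discussion says a widening of inequalities would be weighed against the policy's known benefits. A false widening, or a false narrowing if the drift ran the other way, would therefore matter for policy. The Q4B and Q4C results carry the same risk into the mechanism argument.

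**Working it through.** The article states no sample size, power or significance level, so there is no figure of its own to reproduce. The check asks what the described model returns when the ban does nothing and the gap drifts steadily.

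**Inputs from the article:** data 1994-2016; ban in 2007 (2006 in Scotland, ignored in the closed form); a common trend; education interacted with step and post-ban slope only.

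**Assumptions:** two equal education groups; gap growing by g log-odds per year throughout; equal weight per year; hazard 10%; N person-years at risk per calendar year; two-sided 5% tests.

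**1. Bias.** With balanced groups the gap is fitted by a constant, a step at 2007 and a post-2007 slope. There are 13 pre-ban years (1994-2006) and 10 post-ban years (2007-2016).
- Fitted pre-ban gap = mean of g(t − 1994) over 1994-2006 = 6g
- Gap at 2007 = 13g, so spurious step = 13g − 6g = 7g
- Spurious trend change = g
- Total at 2016 = 7g + 9g = 16g

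| g per year | Step (OR) | Trend change | Total at 2016 (OR) |
|---|---|---|---|
| 0 | 0 (1.00) | 0 | 0 (1.00) |
| 0.01 | 0.07 (1.07) | 0.01 | 0.16 (1.17) |
| 0.02 | 0.14 (1.15) | 0.02 | 0.32 (1.38) |
| 0.03 | 0.21 (1.23) | 0.03 | 0.48 (1.62) |

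A logistic refit to expected probabilities, with Scotland dated 2006, gave step ORs of 1.075, 1.154 and 1.238 for the three non-zero drifts. With education by time added, both ban interactions were 0.000 for every drift tried.

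**2. False-positive rates.** The variance of one year's gap is v = 4/(N × 0.10 × 0.90). For N = 1,000, v = 0.0444.
- SE(step) = √[v(1/13 + 1/10 + 20.25/82.5)] = √(0.0444 × 0.4224) = 0.137
- SE(trend change) = √(v/82.5) = 0.0232
- At g = 0.02: z = 0.14/0.137 = 1.02 and 0.02/0.0232 = 0.86
- Joint 2-df noncentrality = (11.5g)²/[v(1/13 + 1/10)] + (g/SE trend)² = 6.73 + 0.74 = 7.47, where 11.5g is the post-ban mean gap (17.5g) minus the pre-ban mean (6g)

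| N per year | g | Step | Trend change | Joint |
|---|---|---|---|---|
| 200 | 0.02 | 7% | 7% | 18% |
| 500 | 0.02 | 11% | 9% | 39% |
| 1,000 | 0.01 | 8% | 7% | 21% |
| 1,000 | 0.02 | 18% | 14% | 69% |
| 1,000 | 0.03 | 34% | 25% | 97% |
| 2,000 | 0.02 | 30% | 23% | 94% |

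Every rate is 5% at g = 0. Fits with other baseline risks gave 16-40% for the step at g = 0.02 and N = 1,000-2,000. The exact rates therefore depend on inputs the article does not give.

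**3. Precision after the fix.** The added pre-ban slope brings in its own variance (sum of squares 182 over 13 years).
- Step: √[(1/13 + 49/182 + 1/10 + 20.25/82.5)/(1/13 + 1/10 + 20.25/82.5)] = √(0.6916/0.4224) = 1.28
- Trend change: √[(1/82.5 + 1/182)/(1/82.5)] = 1.21

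**4. Placebo dates.** The same algebra with the ban moved five years, at g = 0.02:
- 2002: step = (8 − 3.5)g = 0.09
- 2007: step = 0.14
- 2012: step = (18 − 8.5)g = 0.19
- Trend change = 0.02 at all three dates

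**The case against.** - **The shared trend is inferred.** The article prints no equation and never says outright that education by time is excluded. The wording of Q2 implies that a pre-ban inequality trend was in mind. This is the best argument on the other side. But the article does name its terms: the trend is listed as an overall adjustment, apart from the legislation variables, and only the latter are interacted, for education in both youth and parent models and again for parental smoking. That is a stated structure, and it does not match the Q2 question.
- **The placebo-date rerun is a safeguard.** It could raise suspicion: under pure drift the forward step is larger than the actual one and the trend term does not shrink. But the backward step (0.09 against 0.14) is weaker than the actual one, which is the pattern the plan would take as support for a real ban effect. The rerun also corrects nothing. The later adjustments for tax, legal age and e-cigarettes are not said to vary by education, so they leave gap drift untouched.
- **The size is conditional.** This stands. Without drift there is no bias. Experimentation, escalation and quitting have smaller risk sets, where the separate tests reject much less often. The bias in the estimates is the same at any sample size.
- **Lower-order terms in Q4C.** These are routinely included without being listed, so their absence from the prose is not itself a defect. The missing time interactions are.

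**Conclusion.** The concern holds. As described, the models for Q2, Q3B, Q4B and Q4C hold the pre-ban gap between groups flat and pass any earlier linear drift to the ban terms: all of the yearly drift as a trend change, and about seven years of it as a step. At 0.02 log-odds per year this is OR 1.15 at the ban and 1.38 by 2016 with no ban effect at all, and a joint test that rejects far above 5% at most of the sample sizes considered. These figures rest on the assumed drift, a 10% hazard, two equal groups and the person-years shown. The direction of the false finding follows the direction of the drift. The overall effects in Q1 and Q3A are not at issue here. Because this bears on the project's main question, it should be settled before analysis.

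**What to change.** State in the analysis plan that:
- the Q2 and Q3B models include parental education by overall time trend;
- the Q4B model includes parental smoking by overall time trend;
- the Q4C model includes parental smoking by education by time, with all lower-order terms;
- each ban interaction is read as a departure from that group's own pre-ban trend.

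Reporting the estimated group-by-time terms would show readers how much pre-ban drift there was. The placebo-date rerun should use the same extended models.

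The cost is a short addition to the text and some precision: standard errors of the two-way ban interactions rise by about 28% (step) and 21% (trend change) in the balanced two-group case. The cost for the three-way model was not worked out. Those data are sparser, so Q4C may be best presented as exploratory.
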